## Abstract

**Background:**

Failure of the pancreatic remnant anastomosis to heal following pancreato-duodenectomy is a major cause of significant and life-threatening complications, notably a post-operative pancreatic fistula. Recently, non-randomized trials have shown superiority of a most intuitive anastomosis (Blumgart technique), which involves both a duct-to-mucosa and a full-thickness pancreatic “U” stitch, in effect a mattress stitch, over a standard duct-mucosa technique (Cattell-Warren). The aim of this study is to examine if these findings remain within a randomized setting.

**Methods/Design:**

The PANasta trial is a randomized, double-blinded multi-center study, whose primary aim is to assess whether a Blumgart pancreatic anastomosis (trial intervention) is superior to a Cattell-Warren pancreatic anastomosis (control intervention), in terms of pancreatic fistula rates. Patients with suspected malignancy of the pancreatic head, in whom a pancreato-duodenectomy is recommended, would be recruited from several UK specialist regional centers. The hypothesis to be tested is that a Blumgart anastomosis will reduce fistula rate from 20 to 10 %. Subjects will be stratified by research site, pancreatic consistency and diameter of pancreatic duct; giving a sample size of 253 per group. The primary outcome measure is fistula rate at the pancreatico-jejunostomy. Secondary outcome measures are: entry into adjuvant therapy, mortality, surgical complications, non-surgical complications, hospital stay, cancer-specific quality of life and health economic assessments. Enrolled patients will undergo pancreatic resection and be randomized immediately prior to pancreatic reconstruction. The operation note will only record “anastomosis constructed as per PANasta trial randomization,” thus the other members of the trial team and patient are blinded. An inbuilt internal pilot study will assess the ability to randomize patients, while the construction of an operative manual and review of operative photographs will maintain standardization of techniques.

**Discussion:**

The PANasta trial will be the first multi-center randomized controlled trial (RCT) comparing two types of duct-to-mucosa pancreatic anastomosis with surgical quality assurance.

**Trial registration:**

ISRCTN52263879. Date of registration 15 January 2015.

**Electronic supplementary material:**

The online version of this article (doi:10.1186/s13063-015-1144-9) contains supplementary material, which is available to authorized users.

## Background

### Background and rationale for the study

Pancreato-duodenectomy as a procedure is 100 years old [1–3]. The “Whipple” procedure, as it became known, was refined and standardized during the 1940s to treat head of pancreas cancer [3, 4]. Preservation of the pylorus is now accepted [5–10]. Hence, the current “standard” resection preserves the pylorus with en-bloc resection of the pancreatic head to the right of the portal vein, the extra-hepatic bile duct, the gall bladder, the duodenum and the proximal jejunum. Despite centralization of pancreatic services lowering mortality to below 5 %, morbidity still remains high, often around 50 % for all causes [11, 12]. Failure of the pancreatic anastomosis to heal is a common culprit, with the medical literature quoting a pancreatic leak/fistula rate of between 2 % and in excess of 20 %, [13]. This wide range of leak/fistula rate was due partly to a lack of a consensus definition [12]; however, recently this has been proposed [13] and is beginning to gain support and be quoted in the medical literature. Health economic studies of pancreatic resection from the USA have reported an average length of stay of just over 20 days with an approximate cost of US$1000 per day [14–17]. Edge et al. [14], showed a strong association between complications, length of hospital stay and cost. Resection without complication on average had a hospital stay of 13 days and cost US$30,000. Stay and cost increases proportionally with complications, such that a minor complication increased stay to 18 days (US$43,000) and a major complication to 32 days (US$90,000). Data to 2005 suggest hospital stay is similar but that cost has increased by 63 % [18].

There are a number of techniques of pancreatic remnant reconstruction. Stump closure is a poor option as there are excessive rates of pancreatic fistula, pancreatitis and post-operative exocrine failure [19]. Advocates of pancreato-gastrostomy (PG) quote the superior nature of this technique over that of a jejunal loop, though from a poor literature base [20, 21] with meta-analyses showing conflicting results as studies are combined and both standardized and non-standardized definitions of post-operative pancreatic fistulae (POPF) are used [22, 23]. Anastomosis between the pancreatic stump and the jejunum is regarded as the “standard” technique by many pancreatic surgeons. There are two main ways to perform this: invagination of the pancreatic stump into the jejunum (pancrea*to*-jejunostomy) or anastomosis of the pancreatic duct to the jejunal mucosa (pancrea*tico*-jejunostomy), with covering parenchymal sutures. To date there is a lack of well-designed and well-conducted randomized [24–27] and non-randomized [28–32] studies, specifically looking at these techniques, which have sufficient homogeneity to be compared in meta-analyses. Design issues include the use of non-standardized definitions of POPF, a lack of surgical quality assurance, discontinuous time frames, no stratification for pancreatic consistency or diameter of the pancreatic duct, lack of consideration of the surgical learning curve and irregular use of octreotide and pancreatic duct stents across the groups. Leslie Blumgart (Memorial Sloan Kettering, New York City, NY, USA) has devised a most intuitive anastomosis to use in the setting as it involves both duct-to-mucosa stitches and a full-thickness pancreatic “U” stitch, in effect a mattress stitch. This method of placing the pancreatic parenchymal stitches has significant mechanical advantages over standard techniques as it in effect uses the jejunal mucosa as a pledgelet to minimize sheering forces of the stitches (see Fig. 1).

**Fig. 1 Fig1:**
[figure not shown]
Schematic of the stages of pancreatic anastomosis construction

The rationale for this trial is that an improved method of pancreatic anastomosis should reduce POPF, decrease all complications, hospital stay, cost, improve patient-reported outcomes and promote enhanced recovery programs. Moreover, fewer POPF should enable more patients to take advantage of adjuvant therapy with a possible impact on longer-term survival.

### Preliminary data

Since the description of the “Blumgart” anastomosis, initial results show advantages [33, 34]. Moreover, Kleespies et al. [35] compared a standard Cattell-Warren pancreatico-jejunostomy with a Blumgart anastomosis (BA) technique; this reduced pancreatic leak rate from 13 to 4 % (*p* = 0.03) and overall complications from 31 to 15 % (*p* = 0.015) in favoUr of the BA. Although this study was *not* randomized and was single center, it suggests the usefulness of this technique.

### Objective

To compare the effectiveness of the BA pancreatico-jejunostomy construction versus standard treatment, that is the Cattell-Warren anastomosis (CWA), for patients undergoing an elective pancreatico-duodenectomy in terms of rates of pancreatic fistula.

### Trial design

The PANasta trial is a phase III multi-center study with an internal pilot phase with blinding of patients and outcome assessors (Fig. 2).

**Fig. 2 Fig2:**
[figure not shown]
Flow diagram for the PANasta trial

## Methods/Design

### Study setting

Screening and identification of eligible patients will take place at the research site’s pancreatic multi-disciplinary team (MDT) meeting; all such sites are supra-regional referral centers for suspected pancreatic malignancy. All patients with suspected pancreatic malignancy would undergo standard evaluation: contrast enhanced multi-detector computed tomography (CT) scan ± endoluminal ultrasound (EUS), which will be discussed at the MDT. Patients recommended for resection on the basis of a high likelihood of a malignant lesion will be contacted and provided with a participant information sheet. Informed consent will be obtained by an investigator who should comply with applicable regulatory requirements and should adhere to Good Clinical Practice (GCP) and to the ethical principles that have their origin in the Declaration of Helsinki.

It is not necessary for patients to have a histological diagnosis of malignancy before surgery provided that the MDT has confirmed that the lesion is of sufficient concern to require resection [36].

### Eligibility criteria

#### Inclusion criteria

Patients undergoing an elective pancreato-duodenectomy for presumed malignancy; ability of the subject to understand the nature or consequences of the trial; ability to provide written informed consent and be aged 18 years or older.

#### Exclusion criteria

Patients undergoing extended pancreato-duodenectomy; left, central or total pancreatectomy; arterial resection or multi-visceral resection; previous pancreatic resection; surgery for known chronic pancreatitis; recruitment to any other pancreatic resection trial (at the discretion of the chief investigator/trial team); women of childbearing potential, including women whose last menstrual period was less than 1 year prior to screening; unable or unwilling to use adequate contraception from time of consent up to the day of surgery.

#### Research site criteria

All sites and participating surgeons have expertise in operating upon pancreatic malignancy at high volumes, have confirmed experience with both methods of anastomosis and are willing to randomize patients between the two treatment groups.

### Interventions

#### Trial intervention

Reconstruction of the pancreatic remnant following pancreato-duodenectomy (either Kausch-Whipple or pylorus-preserving) using a “Blumgart” method of pancreatico-jejunostomy.

#### Control intervention

Reconstruction of the pancreatic remnant following pancreato-duodenectomy (either Kausch-Whipple or pylorus-preserving) using a “Cattell-Warren” method of pancreatico-jejunostomy.

Both techniques are regularly used, reported in the medical literature and represent standard methods of reconstruction of the pancreatic remnant. The standardization of the operative techniques will be ensured by using modified methods developed with the MRC ConDuCT-II Trials Methodology Hub [37, 38]:Consensus meetings – a pre-pilot study consensus has been reached regarding the essentials of each anastomosis and the likely key steps, the post-operative management of drains, pancreatic duct stents, the use of octreotide and the timing of operative photographs. This information will be developed into a pilot-phase operative manual and tested in the main phase of the trial.Operative manual – following the feasibility/pilot phase the operative manual will be reviewed and, where applicable, adapted in accordance with the information gained. A finalized operative manual for each anastomosis will be formulated and contain steps that are (a) mandatory to the construction of a safe anastomosis; (b) prohibited for the construction of a safe anastomosis, and (c) flexible steps where the operating surgeon can choose a method (please see Additional file 1).Operative photographs – digital operative photographs will be taken at the key steps during anastomosis construction: preparation of the pancreatic neck prior to anastomosis; insertion of the parenchymal and duct stitches prior to knot-tying and the completed anastomosis. Photographs will be reviewed by the chief investigator and a second reviewer to confirm quality and consistency across sites.

All patients will receive an initial dose of 100 μg of octreotide before surgery. Octreotide should then be administered at 100 μg three times a day subcutaneously on post-operative days 1 to 7. Surgical drains (of any description) must be employed and should be left in place for a minimum of 3 days after surgery. If on post-operative day 3, the drain amylase is normal (i.e., less than ×3 the upper amylase limit for that institution), the drain may be removed (under the direction of the operating surgeon). The use of a pancreatic duct stent is mandatory in all patients. Acquisition of, and upload of operative photographs, as well as other mandatory steps, are recorded in the case report forms (CRFs). This is a surgical trial comparing two different methods of reconstructing the pancreatic remnant following pancreatic head resection. All usual medications and standard of medical care are accepted. There is no requirement to record any medications that are being taken by the patient.

### Outcome measures

The primary outcome measure is leak/fistula rate at the pancreatico-jejunostomy, as measured by presence/content of drain exudate and amylase content analysis within the fluid as per the International Study Group definition: see Table 1 [13]. Secondary outcome measures are: entry into adjuvant therapy/clinical trials of adjuvant therapy; mortality rate; delayed gastric empting [39]; rate of wound infections [40]; rate of pulmonary infection; rate of post-operative fluid collection; operation time; rate of intra- and post-operative bleeding [41]; rate of re-operation; rate of venous thrombo-embolism; hospital stay; generic quality of life and health economic assessments. Patients will complete the cancer- specific questionnaire, the European Organization for Research and Treatment of Cancer (EORTC) QLQ-C30, themselves whereever possible at baseline and in follow-up clinics. Postal assessments may be made as appropriate. Complications [42] that do not have agreed international standards for reporting will be assessed by the Dindo and Clavien classification [43].

**Table 1 Tab1:** Post-operative pancreatic fistula: an International Study Group of Pancreatic Surgery (ISGPF) definition [14]

Grade A	Grade B	Grade C
Without clinical impact	Clinically relevant	Clinical stability may be borderline
Oral nutrition	Partial/total parental/enteral nutrition	Treatment in an intensive care unit in many cases
No antibiotics	Peripancreatic fluid collection possible	Total parental/enteral nutrition
No somatostatin analogues	Abdominal pain, fever, and/or leukocytosis possible	Intravenous antibiotics and somatostatin analogues necessary
No peripancreatic fluid collection	Antibiotics and somatostatin analogues may be necessary	Worrisome peripancreatic fluid collection that requires percutaneous drainage
No delay in hospital discharge	Delay in hospital discharge or readmission may be required.	Extended hospital stay
		Often associated complications and post-operative mortality possible

### Timeline and recruitment

Tertiary regional centers with proven track records will recruit into this trial. All local investigators have confirmed their expertise in both anastomotic techniques and are willing to randomize with clinical equipoise. Recruitment will run over 3 years with a 1-year follow-up. The schedule of trial interventions is shown in Table 2. An internal pilot study will run within the first 6 months. This will run in two centers initially from the day of the trial opening and will inform whether to continue or not dependent upon actual numbers undertaking enrollment as opposed to numbers of patients who would be eligible. Following on from the pilot phase other centers will open.

**Table 2 Tab2:** Schedule of treatments. X demarcates the trial intervention

Visit	Screening	Visit1 (enrolment)	Visit 2 (Randomisation)	Post-operative days 4 and 6	Post operative days 3, 5 and 7	Visit 3 (discharge)	Visit 4 (3m FU)	Visit 5 (6m FU)	Visit 6 (12m FU)	End of Study
	To assess eligibility only (no data to be collected until consent)	Within 4 weeks of surgery	Day of surgery (Day 0)	4 and 6 days post-surgery	3, 5 and 7 days post-surgery	Day of discharge	3 months post surgery (±4 weeks)	6 months post surgery (±4 weeks)	12 months post surgery (±4 weeks)	12 months post-surgery (or earlier due to other cause)
Assessments / Procedures										
Written Informed Form		X^1^								
Assessment of eligibility criteria	X	X								
Suspected date of diagnosis		X								
Demographics (height, weight, etc.)		X				X^2^	X^2^	X^2^	X^2^	
Smoking and alcohol status		X								
Review of Medical History (including symptoms and relevant tests)		X								
Family Medical History		X								
Pregnancy Test		X								
Pancreatic Endocrine Insufficiency status		X			X	X	X	X	X	
Diabetic status		X				X	X	X	X	
Adverse events					X	X	X	X	X	
Octreotide review^3^			X	X	X (Day 3 & 5)					
Surgical drain review			X	X	X	X	X			
Randomisation			X							
CA19-9			X							
Full blood count^4^			X		X (Day 5 ±2 days)	X (Day of discharge −2 days)				
Serum Biochemistry^5^			X		X (Day 5 ±2 days)	X (Day of discharge −2 days)				
Clotting screen^6^			X		X (Day 5 ±2 days)	X (Day of discharge −2 days)				
Blood Sample for translational study^7^			X		X (Day 5 + 2days)					
Histological sample for translational study^8^			X							
Surgical Intervention			X							
Details of surgery			X							
Take Operative photographs			X							
Upload Operative Photographs^9^			X							
Operation time			X							
Intra and post-operative bleeding assessment			X		X	X				
Post- operative fluid collection				X	X	X	X			
Survival status^10^					X	X	X	X	X	X
Delayed gastric emptying assessment					X	X				
Re-operation review					X	X	X	X	X	
Pulmonary infection assessment						X	X			
Surgical site infections assessment					X	X	X	X	X	
Venous thrombo-embolism assessment					X	X	X	X	X	
Fluid collection review (to assess POPF)				X	X	X	X			
Length of initial hospital stay						X				
Re-admission review							X	X	X	
Adjuvant therapy review							X	X	X	
QoL^11^		X				X	X	X	X	
Reason for end of study										X

1. Patient consent does not need to be within 4 weeks of surgery

2. At discharge and follow up weight only to be recorded

3. Initial dose of Octreotide (100ug) to be administered on the evening before surgery (if applicable) then 100ug 3 times daily on the day of surgery and post-operative days 1 to 6

4. FBC (haemoglobin, platelets, absolute neutrophil count, white blood cell count, eosinophils, basophils, lymphocytes, monocytes) to be done pre-operatively either the evening before or morning of surgery and post-operatively on day 5. A window of **±2** days applies to day 5 FBC only and a −2 day window applies at day of discharge

5. Serum biochemistry (sodium, potassium, calcium, urea, creatinine, eGFR, random glucose, albumin, bilirubin, alk.phosphatase, total protein, AST or ALT, GGT and CRP) to be done pre-operatively either the evening before or morning of surgery and post-operatively on day 5. A window of **±2** days applies to day 5 serum chemistry only and a −**2** day window applied at day of discharge

6. Clotting screen (PT and APTT) to be done pre-operatively either on the evening before or morning of surgery and post-operatively on day 5. A window of **±2** days applies to day 5 clotting screen only and a −**2** day window applies at day of discharge

7. Translational blood samples (10ml EDTA tube and 8.5ml SST tube) to be taken pre-operatively either on the evening before or morning of surgery and on post-operative day 5. A window of **+2** days applies to the day 5 translational blood samples

8. Diagnostic H&E slide of the pancreatic neck transection margin will be requested for all patients along with a histological report by the LCTU on a 6 monthly basis. Slides will be held for the duration of the trial and returned at the end

9. Operative photographs should be uploaded on to the LCTU portal immediately after surgery

10. Death due to any cause must be reported by completing an End of Study Form

11. EORTC QLQ-C30 and EQ-5D and EQ-VAS to be completed

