Probably	There is evidence to suggest a causal relationship and the influence of other factors is unlikely
Highly probable	There is clear evidence to suggest a causal relationship and other possible contributing factors can be ruled out

The expected events for this trial along with reporting obligations are detailed in Table 5. Expected events (primary and secondary endpoints) for the trial are exempt from SAE reporting unless they are classified as life-threatening or result in death (grades 4/5). Events that are exempt from SAE reporting should be reported in the relevant sections of the CRFs and *do not* need to be reported as an SAE. All other events that meet the criteria for serious *must* be reported as an SAE and those that do not feature as expected should be classified as *unexpected*. An AE where the causal relationship to the study procedure is assessed by the investigator as “possible,” “probable,” or “highly probable,” is graded as serious and *unexpected* is subject to expedited reporting to the Main Research Ethics Committee (MREC). This is the responsibility of the LCTU.

**Table 5 Tab5:** Expected and unexpected events for serious adverse event (SAE) reporting

Expectedness	Event	Grade 3 and below		Grade 4 and above	
		Report as SAE	Subject to expedite reporting	Report as SAE	Subject to expedite reporting
Expected	Pancreatic fistula (graded as A, B or C)	No	No	Yes	No
	Delayed gastric emptying (graded as A, B, or C)	No	No	Yes	No
	Wound infections	No	No	Yes	No
	Pulmonary Infection	No	No	Yes	No
	Post-operative fluid collection	No	No	Yes	No
	Intra- and post-operative bleeding	No	No	Yes	No
	Re-operation	No	No	Yes	No
	Venous thromboembolism	No	No	Yes	No
	Interventional drainage procedures	No	No	Yes	No
	Extended hospital stay due to delayed surgery	No	No	Yes	No
	Surgical complication related hospital stay	No	No	Yes	No
	New post-operative pancreatic exocrine and or endocrine failure	Yes	No	Yes	No
Unexpected	Any other serious event deemed to be unrelated to the surgical intervention	Yes	No	Yes	No
	Any other serious event deemed to be related to the surgical intervention	Yes	Yes	Yes	Yes

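### The scheduled bleeding assessment stops at discharge, so its window equals hospital stay, which the trial expects to differ by arm; a fixed window from surgery is needed

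*Protocol article*

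**What the plan says.** Outcome measures lists the "rate of intra- and post-operative bleeding" as a secondary outcome. It cites a source for the definition and states no period over which bleeds are counted.

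Table 2 (Timeline and recruitment) schedules the assessments:

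- "Intra and post-operative bleeding assessment": day of surgery, days 3, 5 and 7, discharge. Blank at 3, 6 and 12 months.
- Delayed gastric emptying: also ends at discharge.
- Post-operative fluid collection, pulmonary infection, and the fluid review for POPF: to 3 months.
- "Re-operation review", surgical site infection and "Venous thrombo-embolism assessment": to 12 months.
- "Re-admission review": at 3, 6 and 12 months.
- Adverse events: to 12 months.

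Safety and adverse event reporting asks for all adverse events from surgery until adjuvant therapy starts. Bleeding is an expected event in Table 5: an SAE at grade 4 and above, exempt at grade 3 and below. For exempt events, "Events that are exempt from SAE reporting should be reported in the relevant sections of the CRFs".

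The Background rationale says that an "improved method of pancreatic anastomosis should reduce POPF, decrease all complications, hospital stay" and cost. Hospital stay and entry into adjuvant therapy are themselves secondary outcomes.

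**The concern.** A complication rate is comparable between arms only if patients in both arms are at risk of being counted for the same length of time. Here the scheduled counting period ends at discharge, which happens after randomization and may be affected by the anastomosis. If the intervention works as hoped, its patients leave hospital sooner and their bleeding window closes sooner. With equal true bleeding, the arm with the shorter stay would show fewer bleeds. The article gives no reason for scheduling bleeding differently from the complications followed to 3 or 12 months.

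At stake is one secondary safety comparison: some under-recording of late bleeds, and a possible tilt with a known direction. The sample size and the primary fistula analysis are not involved.

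**Working it through.** The article states no figure for bleeding, so there is none to reproduce. The check has two parts.

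**1. Routes by which a bleed after discharge could be recorded**

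- Bleeding assessment: not scheduled after discharge.
- CRF entry for exempt events (grade 3 and below): required, with no visit limit stated, but no bleeding assessment is scheduled after discharge to prompt it.
- General adverse event: reportable, but only until adjuvant therapy starts, which is another outcome expected to differ by arm. It is graded on the general severity scale of Table 3, whereas the bleeding outcome cites its own source.
- SAE: grade 4 and above.
- Re-operation and re-admission reviews: to 12 months. A bleed managed without either would not appear there.

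The article does not say whether records from the last three routes count toward the bleeding rate.

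**2. Size of the tilt if only the scheduled assessment counts**

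Inputs from the article: stays of 13 days without complication, 18 with a minor and 32 with a major complication (Background; US data); fistula rates of 20 % in control and 10 % under the trial hypothesis (Sample size). Assumptions: bleeding risk is equal in the two arms, and every patient without a fistula stays 13 days.

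Mean window = 13 + (fistula rate × extra days).

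- Fistula treated as a major complication (19 extra days): control 13 + 0.20 × 19 = 16.8; Blumgart 13 + 0.10 × 19 = 14.9; ratio 0.887.
- Fistula treated as a minor complication (5 extra days): control 13 + 0.20 × 5 = 14.0; Blumgart 13 + 0.10 × 5 = 13.5; ratio 0.964.

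Under a constant post-operative hazard the bleeding rate is roughly proportional to the window, giving an apparent reduction of 4 to 11 %.

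A constant hazard is not given in the article, so bleed timing was varied. Assume exponential time to bleed. The share of 90-day bleeds captured by discharge day t is (1 − exp(−t/mean)) / (1 − exp(−90/mean)):

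| Mean time to bleed | Day 13 | Day 18 | Day 32 |
|---|---|---|---|
| 5 days | 0.926 | 0.973 | 0.998 |
| 10 days | 0.728 | 0.835 | 0.959 |
| 20 days | 0.483 | 0.600 | 0.807 |

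Weight these by the fistula rates (control 80 % at day 13 and 20 % later; Blumgart 90 % and 10 %). For a mean of 20 days and a major-complication stay:

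- control: 0.80 × 0.483 + 0.20 × 0.807 = 0.548
- Blumgart: 0.90 × 0.483 + 0.10 × 0.807 = 0.515
- ratio: 0.94

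The same sum gives 0.97 for a mean of 10 days and 0.99 for a mean of 5 days. With minor-complication stays the ratios are 0.98, 0.99 and 0.99 for means of 20, 10 and 5 days.

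A starker contrast, with one whole arm leaving on day 13 and the other on day 18, gives ratios of 0.81, 0.87 and 0.95 for means of 20, 10 and 5 days. That 5-day gap is wider than the 0.5 to 1.9 days implied by the fistula hypothesis.

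On an assumed true bleeding rate of 10 %, a 4 to 11 % relative reduction is 0.4 to 1.1 percentage points. The standard error of the difference at 208 per group is √(2 × 0.10 × 0.90 / 208) = 0.029, or 2.9 points.

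A window of fixed length from surgery gives a ratio of 1.00 under every one of these timings.

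**The case against.** A reader might infer that bleeds after discharge are lost, or that those below grade 4 are hidden from the monitoring committee. The documents do not support either. Adverse events are reportable until adjuvant therapy starts, exempt events must be entered in the CRF, grade 4 and 5 bleeds are SAEs, and the adverse event, re-operation and re-admission rows run to 12 months. No sentence excludes these records from the bleeding rate, and none limits the committee to SAEs or to the bleeding form. Table 2 says when an assessment is scheduled, which is not the same as defining the endpoint, and a condensed article may leave the endpoint's data sources to the full protocol or the analysis plan. Delayed gastric emptying has the same cut-off, so in-hospital assessment may have been intended.

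The size is also open to attack. Bleeds may cluster early, intra-operative bleeds are captured in both arms, the stays are US figures, and with all-cause morbidity around 50 % many patients without a fistula would stay longer than 13 days. The expected tilt is well inside the sampling error.

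All of this stands, and it limits the claim. It does not remove the point. The schedule is printed in full, and an analysis plan cannot recover an assessment that was never scheduled. The substitute routes have gaps of their own, and one of them closes at another outcome expected to differ by arm.

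**Conclusion.** The point holds in a limited form. The dedicated bleeding assessment ends at discharge, so its window is the length of stay. Bleeds after discharge fall outside that assessment, and the article does not say whether bleeds recorded elsewhere count.

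Bias toward the arm discharged earlier is conditional. It needs a difference in stay between arms, and bleeds after discharge that are not otherwise counted. A shorter stay with Blumgart is the protocol's expectation, not a result, so it would be wrong to say that this arm is certainly favoured. Given both conditions the direction is clear but the size is not. The 4 to 11 % figure illustrates a constant post-operative hazard with the article's stays; under the earlier bleed timings assumed above, the same stays and fistula rates give about 1 to 6 %. This is a cheap improvement to one secondary outcome. The primary endpoint is unaffected.

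**What to change.** - Mark the bleeding row of Table 2 at Visit 4 (3 months), and ask there about bleeds since discharge.
- Define the outcome as any intra- or post-operative bleed, by event date, within one fixed number of days from surgery in both arms, for example day 90. The visit itself should not be the cut-off: its ±4 weeks spans about day 63 to day 119 (91 ± 28).
- For patients seen before the cut-off day, complete the window from the later re-admission, re-operation and adverse event reviews.
- State that adverse event, re-admission and re-operation records feed the outcome.
- Report the in-hospital bleeding rate as supplementary.

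The cost is one extra CRF item at an existing visit and one line in the schedule. No visit or procedure is added and the sample size does not change. The reported bleeding rate may be slightly higher.
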